**c. Statistical Analysis.**

All analyses will allow appropriately for the clustering. We will use random effects models to account for correlation within polyclinic, as is recommended for cluster randomized trials. Results will be reported as mean differences. We will derive 95% confidence intervals and Wald tests of the null hypothesis of no association between intervention groups. Effect modification will be addressed by stratification and by formally testing for statistical interaction by introducing appropriate cross-product terms. We will initially examine results stratified by sex to ensure comparability, before we consider combining results for boys and girls.

It is well known that “per-protocol” analyses of randomized trials, in which participants are grouped according to the intervention they received, rather than that to which they were randomized, may be seriously biased. It is for this reason that the primary analyses for this study will be based on intention-to-treat. However, this approach may substantially underestimate the effect of the true exposure of interest (breastfeeding exclusivity and duration), since there was not complete contrast of breastfeeding status between the randomized groups: many intervention mothers did not exclusively breastfeed for 6 months, whereas some control mothers did. There is a substantial statistical literature showing that causal effects of interventions may be validly estimated from randomized trials, allowing appropriately for non-compliance with the intervention.^152-155^ Thus, in secondary analyses, we will apply instrumental variable methods to estimate the causal effect of the difference in breastfeeding exclusivity and duration achieved between the two randomized groups on our outcomes. In this approach, we will use randomization status as the ‘instrument’ that is independent of any confounders of the exposure-outcome relationship, and is related to the outcomes only via the exposure. We will thus validly estimate the unbiased effect of breastfeeding itself on cognition, vision, and lung function. Although these analyses will address the attenuation of the effect of breastfeeding that is inevitable in intention-to-treat analyses, they are unlikely to increase the power of the study, so sample size calculations are not affected.

**2.3.6. Power**

Based on follow-up in PROBIT I-III, we expect 14,000 participants in PROBIT IV. We calculated detectable differences based on this number of subjects in 31 clusters, an intention-to-treat (ITT) analysis, 80% power, 5% significance, and used a realistic value (0.01) of the intra-cluster correlation coefficient (ICC) based on the ICCs of outcomes in PROBIT I-III. The effective sample size in PROBIT IV, allowing for the clustered design, is the total number of anticipated participants (14,000) divided by the design effect (*Deff*), where *Deff* = 1+(*n*-1)×ICC and *n* is the average number of individuals per cluster (n=14,000/31=451).^156^ Thus, the design effect for an ICC of 0.01 is 1+4.5=5.5 and the effective sample size is 2,500 children (14,000/5.5). Expected means and SDs for each outcome were taken from childhood cohorts of similar age. Mean detectable differences, assuming exposure groups are dichotomized at the midpoint, are calculated as the product of the SD of each variable and the standardized difference (i.e. 0.1 given an effective sample size of 2,500^157^). For the categorical atopic eczema outcome at the 16-year follow-up (flexural eczema on skin examination), the study has 94% power at the 5% significance level to detect a 50% reduction in atopic eczema prevalence between the two study groups, similar to PROBIT I.^21^

**Table 5** shows the mean differences that can be detected in the comparison of the two randomized arms by ITT and the corresponding effect due to breastfeeding that would have to be present to achieve those ITT differences. The breastfeeding effect is based on the difference in exclusive breastfeeding at 3 months of 43% in the intervention arm and 6% among controls, and is derived by dividing the ITT differences by 0.37=37% (the difference in exclusive breastfeeding in the 2 arms). For comparison, published differences are shown. The sample size is adequate for detecting important differences in the outcomes (**Table 5**). If we fail to find associations in the ITT analysis, the study is powered to have narrow confidence intervals (CIs) around null estimates. The 95% CIs for zero mean differences, assuming an effective sample size of 1250 in each arm ((14,000/Deff) ÷ 2) and means/SDs in Table 2, would be: cognitive score ± 1.2; FEV_1_ ± 40mls; FVC: ± 45mls; PEFR: ± 60mls/s.

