Our current proposal is based on the 15-16 year follow-up of children enrolled in PROBIT. Our hypotheses build on important findings from a previous follow-up of PROBIT children. In an intention-to-treat analysis, 6.5-year olds in the intervention arm had a 7.5 point advantage in verbal intelligence quotient (IQ) and higher teacher rated reading and writing *vs.* controls. At that age, most children had recently started school, but IQ is sensitive to environmental factors such as length of schooling. Thus, it remains unclear whether breastfeeding has an enduring effect on IQ. Furthermore, the pediatricians administering the IQ tests were not blinded to the children’s randomization status. In our current proposal, we plan to use self-administered tests of cognition and language, which will minimize any administrator bias. Also at age 6.5 years, the PROBIT intervention was not associated with asthma assessed by questionnaire (odds ratio: 1.2; 95% CI: 0.7-1.9), but the wide confidence interval does not exclude potentially important protective or adverse effects. In the current proposal, we include spirometric lung function measures, which index susceptibility to, and consequences of, asthma. Spirometry provides objective and continuous outcome measures, increasing study power. The PROBIT intervention was associated with a reduced risk of atopic eczema at 12 months (odds ratio: 0.54, 95% CI, 0.31-0.95), but was not associated with eczema assessed by questionnaire at 6.5 years (odds ratio: 1.0, 95% CI, 0.5-1.8). However, the reported prevalence of eczema at age 6.5 was also extremely low (1%). We hypothesized that parents may not have reported cases of eczema that were not diagnosed by a doctor. In this proposal, we plan to minimize such underreporting by training the study pediatricians to conduct physical examinations of participant’s skin to identify atopic eczema around the participant’s eyes, neck, elbows, knees or ankles. Such examinations should provide a more systematic approach to identifying true cases of atopic eczema.

Also at age 11.5 years, the PROBIT intervention was not associated with measured obesity (odds ratio: 1.17 (95% CI, 0.97 to 1.41) or blood pressure (mean difference between intervention vs control arms:

1.0 mmHg (95% CI: -1.1 to 3.1) for systolic and 0.8 mmHg (-0.6 to 2.3) for diastolic blood pressure, but the wide confidence interval does not exclude potentially important protective or adverse effects.

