Nevertheless, these findings have been controversial and merit further investigation. Our current proposal maintains the strengths of earlier work within PROBIT, i.e. the large sample size and randomized design, while improving on the prior limitations, namely the young age at outcome assessment and imprecisely measured outcomes. An observational study and meta-analysis^19^ found that a positive association of breastfeeding with child IQ became negligible after controlling for parental IQ. Other studies that controlled for maternal IQ, however, report persistent, albeit attenuated, IQ benefits.^16,20^ In an RCT like PROBIT, parental IQ should be distributed randomly between treatment groups, as demonstrated for other measured baseline characteristics,^21^ and thus should not confound the intervention effect. The effect sizes for IQ at age 6.5 in PROBIT were imprecisely measured, due to high within-pediatrician clustering of IQ values across the 31 trial sites.^22^ While analyses based on the blinded audit and teacher ratings suggest the direction of the observed differences is robust, we do not know whether the large difference in verbal IQ arose by chance or a systematic overestimate of verbal IQ in the experimental group. The smaller differences seen in the blinded audit and teacher ratings may more closely estimate the true effect. All pediatricians were trained, monitored, and audited in their administration of the WASI, and no beneficial intervention effects were observed for other outcomes,^23-25^ equally subject to systematic error, providing some reassurance that the pediatricians’ assessments of outcomes were unbiased. Nevertheless, the pediatricians who administered the WASI were not blinded to the trial arm of the children they examined, as many had contributed to the original intervention by providing postnatal support and encouragement of prolonged, exclusive breastfeeding.^21^ It is possible that the pediatricians at the intervention sites may have differentially administered or scored the WASI. In addition, about 20% of children seen at age 6.5 years had yet to start school, and they may have had difficulty completing the IQ test, potentially generating random measurement error.

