**f. Outcomes at age 11 years (PROBIT III)**

***Table 4: Intra-class correlation coefficients (ICC) for measurements taken in PROBIT III***

| *Measurement* | *ICC* |
| --- | --- |
| Standing height | 0.03 |
| Sitting height | 0.03 |
| Weight | 0.02 |
| Bioimpedance | 0.01 |
| Mid-upper arm circumference | 0.03 |
| Systolic blood pressure | 0.12 |
| Waist circumference | 0.07 |
| Hip circumference | 0.03 |
| Head circumference | 0.10 |
| Triceps skinfold thickness | 0.12 |
| Subscapular skinfold thickness | 0.04 |
| Glucose | 0.08 |

At 11.5 years (PROBIT III), we investigated effects of breastfeeding on growth and cardio-metabolic risk factors. Pediatricians performed anthropometric measurements on mothers and children, and collected fasting blood via fingerstick. We have completed all study visits and await final data entry and results of laboratory assays. The participation rate - 13,891 children were seen – attests to our ability to maintain excellent follow-up and thus minimize retention bias. Intra-class correlation coefficients were extremely low for all measured outcomes (**Table 4**), indicating valid measurements with a low degree of clustering.

In an interim intention-to-treat analysis (n = 12,374), cluster-adjusted mean differences in experimental vs. control groups were essentially null: 0.16kg/m^2^ (95% CI: -0.08, 0.40) for BMI; 0.43% (-0.15, 1.01) for body fat; 0.33cm (-1.25, 1.92) for waist circumference; 0.11mm (-1.53, 1.74) for triceps skinfold thickness; 0.62cm (-0.40, 1.64) for height; and 1.12mmHg (-1.06, 3.30) for systolic blood pressure.^141^ The odds ratio for obesity (experimental vs. control arms) was 1.19 (0.95, 1.50). We found similar null results for maternal postpartum adiposity.^142^ We now have a number of papers in progress presenting results of the intention-to-treat analysis of the anthropometric and biochemical study outcomes. Our joint experience leading PROBIT III yields several important messages: we have demonstrated our successful collaboration in leading a PROBIT outcome visit; we achieved high rates of follow-up with little evidence for bias in follow-up or clustering in outcome assessments; and we require 4 years of funding to allow for complete data collection and analysis.

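### Power is planned for every outcome on the lowest ICC in the protocol's own table; for systolic blood pressure the detectable difference is understated about 3-fold

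*Protocol*

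**What the plan says.** Protocol section 2.3.6 states that "we expect 14,000 participants in PROBIT IV" and bases the detectable differences on "this number of subjects in 31 clusters, an intention-to-treat (ITT) analysis, 80% power, 5% significance". The design effect uses the mean cluster size, which "is the average number of individuals per cluster (n=14,000/31=451", and for the ICC the authors "used a realistic value (0.01) of the intra-cluster correlation coefficient (ICC) based on the ICCs of outcomes in PROBIT I-III". This gives a design effect of 5.5, an effective sample size of 2,500 and a standardized detectable difference of 0.1. Table 5 then lists detectable differences, including 1.15 mmHg for systolic and 0.82 mmHg for diastolic pressure. The text concludes that the sample size is adequate and that "the study is powered to have narrow confidence intervals (CIs) around null estimates". Null half-widths are given for the cognitive score, FEV1, FVC and PEFR only.

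Table 4 (section 2.3.3 f) prints the ICCs from PROBIT III, including "Systolic blood pressure | 0.12". The Specific Aims report the 11.5-year intention-to-treat result as "1.0 mmHg (95% CI: -1.1 to 3.1) for systolic", with a diastolic interval of -0.6 to 2.3 mmHg. Section 2.1.1 describes the 6.5-year IQ effects as "imprecisely measured, due to high within-pediatrician clustering of IQ values across the 31 trial sites".

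**The concern.** The planning ICC is presented as grounded in earlier phases of the trial, but the only ICCs the protocol prints do not support it. The value 0.01 is the minimum of Table 4, not a typical figure, and it is applied to blood pressure although systolic pressure has its own printed value twelve times larger.

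With some 450 children per cluster the design effect is almost proportional to the ICC, so this one input drives the effective sample size, the detectable differences and the stated 80% power. If it is too low for an outcome, Table 5 promises sensitivity that 31 clusters cannot give, and a null finding could be read as ruling out effects that the design cannot rule out. The Specific Aims already describe the 11.5-year blood pressure intervals as too wide to exclude important effects. Section 2.3.6 expects much better from about the same number of children in the same clusters.

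**Working it through.** **Inputs.** N = 14,000, 31 clusters, 80% power, 5% significance (taken as two-sided, since sidedness is not stated), ICC 0.01 and equal effective arms, all from section 2.3.6. SDs from Table 5: 15 (cognitive score), 9.6 mmHg (systolic). Table 4 ICCs in ascending order: 0.01, 0.02, 0.03 (four times), 0.04, 0.07, 0.08, 0.10, 0.12 (twice). Median 0.035, mean 0.057.

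**Formulas.** m = 14,000/31 = 451.6; Deff = 1 + (m - 1) × ICC; effective N = 14,000/Deff; standardized detectable difference = (1.96 + 0.8416) × 2/√(effective N); null half-width = 1.96 × SD × 2/√(effective N).

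**The plan's own figures.** Deff = 1 + 450.6 × 0.01 = 5.51 and effective N = 2,543 (stated 5.5 and 2,500). With 1,250 per arm, the cognitive half-width is 1.96 × 15 × √(2/1,250) = 1.18 (stated 1.2). The arithmetic reproduces. One side issue: 2.8016 × 2/√2,500 = 0.112, which the plan rounds down to 0.1; power at exactly 0.1 SD is about 71%.

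**Same formulas at the Table 4 ICCs.**

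| ICC | Deff | Effective N | Detectable (SD) | Ratio to ICC 0.01 | Power for 0.1 SD |
|---|---|---|---|---|---|
| 0.01 | 5.5 | 2,543 | 0.111 | 1.00 | 71% |
| 0.02 | 10.0 | 1,398 | 0.150 | 1.35 | 46% |
| 0.03 | 14.5 | 964 | 0.180 | 1.62 | 34% |
| 0.035 (median) | 16.8 | 835 | 0.194 | 1.75 | 30% |
| 0.04 | 19.0 | 736 | 0.207 | 1.86 | 27% |
| 0.07 | 32.5 | 430 | 0.270 | 2.43 | 18% |
| 0.08 | 37.1 | 378 | 0.288 | 2.59 | 16% |
| 0.10 | 46.1 | 304 | 0.321 | 2.89 | 14% |
| 0.12 | 55.1 | 254 | 0.351 | 3.16 | 12% |

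**Systolic pressure at its own ICC of 0.12.** Detectable difference = 9.6 × 0.351 = 3.37 mmHg. Against the stated 1.15 that is 3.37/1.15 = 2.9-fold. Power for 1.15 mmHg: SE = 9.6 × 2/√254 = 1.20; 1.15/1.20 = 0.955; Φ(0.955 - 1.96) plus a negligible opposite tail = 16%.

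**Check from the trial's own intervals, needing no ICC or SD.**
- Systolic: SE = (3.1 + 1.1)/3.92 = 1.07; × 2.8016 = 3.0 mmHg, or 2.6 times the stated 1.15.
- Diastolic: SE = (2.3 + 0.6)/3.92 = 0.74; × 2.8016 = 2.07 mmHg, or 2.5 times the stated 0.82.
- Divided by 0.37, as section 2.3.6 does, these become 3.0/0.37 = 8.1 and 2.07/0.37 = 5.6 mmHg. Both exceed the maximum published differences in Table 5 (6.5 and 3.4).

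With SD 9.6 and n = 13,879 (registration record), the systolic SE implies an ICC of about 0.095, close to the 0.12 in Table 4.

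**Outcomes without a printed ICC (illustration only).** For the cognitive score, the detectable difference and null half-width would be 1.7 and ±1.2 at ICC 0.01, 2.9 and ±2.0 at 0.035, and 5.3 and ±3.7 at 0.12.

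**The case against.** A reader might infer that everything in Table 5 is understated by 2 to 3 times. The documents do not support that. Doubling needs an ICC of about 0.047, and only five of the 12 values exceed it. Three of those five (triceps skinfold, head circumference, glucose) are not among the PROBIT IV outcomes. The Table 4 measures carried forward are bioimpedance 0.01, weight 0.02, standing height 0.03, waist 0.07 and systolic pressure 0.12, with median 0.03 and a ratio of 1.62. Bioimpedance, the source of the fat and fat-free mass measures, has exactly the planning value. The interim 11.5-year BMI interval in section 2.3.3 f, with Table 5's SD of 2.0, implies an ICC of about 0.027.

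A reader might also infer that the null intervals for cognition and spirometry are wrong. No ICC is printed for either, so that would be analogy. The 6.5-year IQ intervals do imply an ICC near 0.4 (assuming SD 15, n = 13,889 and equal arms). But those tests were given and scored by pediatricians, and section 2.1.1 says that PROBIT IV replaces them with self-completed, automatically scored testing. That is a fair reason to expect less clustering, though not evidence for 0.01. It does not extend to blood pressure, spirometry, acuity or skin examination, which pediatricians carry out.

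It can also be said that Table 4 covers PROBIT III only, whereas the ICC is attributed to phases I to III. No ICC from phase I or II is printed, and the one statement on phase II clustering, for IQ, says it was high.

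Finally, the cohort is fixed, and section 2.3.5 c analyses with random-effects models and cluster-adjusted intervals, so no estimate or test depends on 0.01. That stands and limits the harm, but it does not correct the stated power.

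**Conclusion.** The point holds, and section 2.3.6 needs correcting. The claim that 0.01 is realistic and drawn from earlier phases conflicts with Table 4, where it is the minimum of 12 values. Across the other 11 ICCs, detectable differences are 1.35 to 3.16 times those at ICC 0.01: 1.75 at the median and 1.35 to 1.6 for weight and height.

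For blood pressure the error is shown directly. Systolic is about 3.4 mmHg from its ICC, or 3.0 mmHg from the 11.5-year interval, against 1.15. Diastolic is about 2.1 mmHg against 0.82. The claim of adequate size is not supported for these two outcomes. For cognition, spirometry, acuity and eczema, understatement is possible but not demonstrated.

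The figures assume equal arms, equal cluster sizes, a normal approximation (t quantiles on 29 degrees of freedom would add about 3.5%), Table 5's SDs where an ICC is used, and clustering at 15-16 years similar to that at 11.5 years.

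**What to change.** 1. Recompute the blood pressure and anthropometry rows of Table 5 with the Table 4 ICCs. Use the 11.5-year standard errors as a check, and as the source for diastolic pressure, which has no printed ICC.
2. For the cognitive score, spirometry, acuity and eczema, show detectable differences, eczema power and, where quoted, null half-widths over an ICC range of 0.01 to 0.12. Say why a lower value may be expected for self-completed cognitive testing.
3. Remove the description of 0.01 as realistic, and qualify the statements that the sample size is adequate and the null intervals narrow, outcome by outcome.
4. In the same recalculation, use the unrounded 0.111 to 0.112 SD in place of 0.1.

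The cost is a revised table and some wording. No participants, visits or analyses are added. The only downside is that the stated precision becomes less favourable.

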***Vision****.* We will use the LogMAR-Crowded test (<http://www.keeler.co.uk>) to measure vision without optical correction, visual acuity with optical correction (if present) and pinhole acuity in each eye, to determine if any deficit in vision is refractive. A vision cut-off (LogMAR 0.2, equivalent to worse than 6/9 Snellen acuity) will be used to define myopia; this threshold has high sensitivity (>90%) and specificity in identifying myopia,^126,147^ and that 91% of those with this level of vision at 16 years will be myopic in later life.^148^ The definition of myopia will be validated in a subset of children from the largest polyclinic (n=1000) using open field auto-refraction with a distant fixation target (Maltese cross at 5 meters) to stabilize accommodation without need for pharmaceutical cycloplegia (which could otherwise compromise participation).

***Atopic eczema.*** We will identify cases of atopic eczema through physical skin examinations conducted by the PROBIT study pediatricians, and collect additional data on eczema symptoms and skin health through questions from the International Study of Allergy and Asthma in Children (ISAAC) questionnaire. Study pediatricians will examine PROBIT participants for signs of flexural dermatitis around the eyes, the back of the neck, the front of the elbows, the back of the knees, and the front of the ankles. Evidence of flexural dermatitis upon exam at any of the 5 examination sites is sufficient for a diagnosis of atopic eczema.

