**b. Exposure, outcomes, and covariates**

The exposure will be randomization to the breastfeeding promotion intervention or to the control group. The expected sample size is 14,000 children from 31 polyclinics.

The main neurocognitive outcomes will be the *Mindstream* scores standardized to an IQ scale (mean 100, SD 15) for memory; executive function; visual-spatial accuracy; verbal function; attention; information processing; motor skills; and a global cognitive score. Vision will be assessed using LogMAR acuity, analyzed as a continuous variable (given its more normal distribution compared to Snellen acuity measures); prevalence of reduced LogMAR visual acuity will also be considered between intervention groups. Atopic eczema outcomes will be evidence of flexural dermatitis around the eyes, the back of the neck, front of the elbows, back of the knees, or ankles, as identified by a trained PROBIT pediatrician; secondary atopic eczema outcomes will include responses to the skin questions from the ISAAC questionnaire. Respiratory function outcomes will be PEFR, FEV_1_ and FVC, each expressed as internal z-scores adjusted for height, age and sex. Adiposity outcomes will be body mass (BMI), fat mass (FMI), and fat-free mass (FFMI) indices, waist-to-height ratio and overweight as BMI between the 85th to <95th percentiles and obesity as BMI at or above the 95th percentile, based on the Centers for Disease Control and Prevention (CDC) 2000 age- and sex-specific reference data. Blood pressure outcomes as continuous measures of systolic and diastolic blood pressure.

Since the number of polyclinics randomized in PROBIT (31) was relatively small, imbalances in baseline covariates sufficient to confound the effect estimates may have occurred. We will therefore conduct a secondary analysis in which we control for any predictors of our outcomes (unadjusted P<0.1) that are also found to be associated (P<0.1) with randomization status. To date, PROBIT analyses suggest that this circumstance is unlikely to occur (see **Table 1**); no evidence of confounding by individual-level covariates was evident in PROBIT I, II or III.^17,21^ The main hospital-level potential confounders are geographic region and urban versus rural location.

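### The 0.1 SD rows of Table 5 do not have 80% power at the protocol's own ICC: the detectable difference is about 0.111 to 0.113 SD, mostly through rounding, with a small addition from unequal clusters

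*Protocol*

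**What the plan says.** Section 2.3.6 of the protocol states that "we expect 14,000 participants in PROBIT IV", and Section 2.3.5.b spreads them over 31 clusters: "The expected sample size is 14,000 children from 31 polyclinics". The calculation "used a realistic value (0.01) of the intra-cluster correlation coefficient (ICC") and the formula Deff = 1+(n-1)×ICC, where n "is the average number of individuals per cluster (n=14,000/31=451"). From this, "the design effect for an ICC of 0.01 is 1+4.5=5.5 and the effective sample size is 2,500 children (14,000/5.5"). The stated conditions are "an intention-to-treat (ITT) analysis, 80% power, 5% significance". Each detectable difference in Table 5 is the SD of the outcome times "the standardized difference (i.e. 0.1 given an effective sample size of 2,500").

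The vision paragraph of Section 2.3.4.b plans to validate the myopia definition in "a subset of children from the largest polyclinic (n=1000"). Section 2.3.5.c specifies random effects models by polyclinic for the analysis.

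**The concern.** Two steps in the power section favour the design.

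- The design effect with the mean cluster size is exact only when all clusters are the same size. The protocol does not say that it assumes this, and a polyclinic with about 1,000 children has more than twice the mean.
- The standardized difference of 0.1 is a rounded figure. At an effective sample size of 2,500, 80% power needs more than that.

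The protocol relies on Table 5 when it calls the sample size adequate. If the differences are stated as smaller than the design can detect with 80% power, a null result for cognition or lung function will look more informative than it is.

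**Working it through.** **Inputs.** N = 14,000, 31 clusters, ICC 0.01, 80% power and 5% significance (Sections 2.3.5.b and 2.3.6). I take the test as two-sided and the arms as equal; Section 2.3.6 uses 1,250 effective children per arm. Largest clinic: 1,000 (Section 2.3.4.b).

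**The protocol's own figure.** Mean size = 14,000/31 = 451.6. Deff = 1 + 450.6×0.01 = 5.51. Effective n = 14,000/5.51 = 2,543. The stated 5.5 and 2,500 reproduce; 2,543 was rounded down.

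**Detectable difference.** d = (1.960+0.842)×2/√(effective n).

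- Effective n 2,500: d = 5.603/50 = 0.112 SD, or 1.68 cognitive points. Power at 0.1 SD is 71%.
- Effective n 2,543 (equal clusters): d = 0.111 SD, or 1.67 points. Power at 0.1 SD is 71%.

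So the 0.1 falls short before any inequality in cluster size is considered.

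**Adding the documented large clinic.** The smallest spread compatible with one clinic of 1,000 makes the other thirty equal, at 13,000/30 = 433 each. This gives CV = 0.22.

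- All children weighted equally: Deff = 1+((1+CV²)×451.6-1)×0.01 = 5.73; effective n = 2,444; d = 0.113 SD (1.70 points); power at 0.1 SD about 70%.
- Random-effects weighting: effective n = Σ mᵢ/(1+(mᵢ-1)×0.01) = 1,000/10.99 + 30×433.3/5.323 = 91 + 2,442 = 2,533; d = 0.111 SD.

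**Wider spread.** The protocol gives no other clinic sizes, so these CVs are assumptions. The random-effects column for CV 0.4 and 0.8 uses gamma-distributed sizes.

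| CV | Random effects: effective n, d, points | Equal weighting: effective n, d, points |
| --- | --- | --- |
| 0.22 (documented minimum) | 2,533, 0.111 SD, 1.67 | 2,444, 0.113 SD, 1.70 |
| 0.4 (assumed) | about 2,480, 0.113 SD, 1.69 | 2,248, 0.118 SD, 1.77 |
| 0.8 (assumed) | about 2,280, 0.117 SD, 1.76 | 1,667, 0.137 SD, 2.06 |

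**Row by row in Table 5** (stated, then needed with equal clusters and with the documented imbalance under equal weighting).

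- Cognitive score: 1.5; 1.67 to 1.70
- FEV1: 48 ml; 53 to 54
- FVC: 58 ml; 64 to 65
- PEFR: 80 ml/s; 89 to 91
- LogMAR: 0.02; 0.022 to 0.023 (not visible at the two decimals printed)
- Systolic pressure: 1.15, which is 1.15/9.6 = 0.120 SD; 1.07 to 1.09
- Diastolic pressure: 0.82, which is 0.82/6.8 = 0.121 SD; 0.76 to 0.77

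The column for the breastfeeding effect divides by 0.37 and moves in proportion: 1.67/0.37 = 4.5 cognitive points, where 4.1 is stated.

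**Null confidence intervals.** At effective n 2,444 the half-width is 1.96×SD×2/√2,444: cognition 1.19 (stated 1.2), FEV1 38 (40), FVC 46 (45), PEFR 63 (60). These agree with the stated values about as well as the values at 2,500 do (1.18, 38, 45, 63).

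**The case against.** The best defence is that the clustering arithmetic reproduces and was rounded down, which almost absorbs the documented imbalance: 2,444 is only 2.2% below 2,500. The planned random effects model gives large clinics less weight, and on that basis the effective n is 2,533, above the stated figure. The n=1000 is also ambiguous. It may be the subset or the clinic, and if it counts enrolled children of whom 82% return (820), the equal-weight formula gives 2,497. All of this stands. A reader might infer from the large clinic that the design really needs 1.8 to 2.1 cognitive points and has only 66 to 53% power at 0.1 SD. The documents do not support that: those figures need a CV of 0.4 to 0.8, which is nowhere given, and equal weighting of children, which is not the planned analysis.

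It could also be said that 5% significance is not explicitly two-sided. A one-sided 5% test would give (1.645+0.842)×2/50 = 0.099 SD, which is the stated 0.1. But the analysis reports 95% confidence intervals, and the aims leave room for adverse as well as protective effects. The stated 94% power for eczema also fits a two-sided test: 6.3% against 3.3% with 1,250 per arm gives z = 0.030/0.00853 = 3.52, and 3.52-1.96 = 1.56, or 94%. One-sided it would be 97%.

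None of this rescues 0.1 SD at 80% power for a two-sided test.

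**Conclusion.** The point holds as a minor correction. At ICC 0.01 and two-sided 5%, the design needs 0.111 to 0.113 SD for 80% power, and has about 70% power at the stated 0.1 SD. With equal clusters the gap from 0.1 is already 0.011 SD. The documented imbalance adds less than 0.001 SD under the planned model and about 0.002 SD under equal weighting. An assumed CV of 0.8 would bring the planned model to 0.117 SD.

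The cognitive, FEV1, FVC, PEFR and LogMAR rows are affected. It would go too far to call all of Table 5 too favourable on this ground. The blood pressure rows, at about 0.12 SD, are still met at the documented imbalance, and under equal weighting up to a CV of about 0.45. The BMI row (0.024/2.0 = 0.012 SD) is wrong for a separate reason. The effective sample size and the null intervals hold approximately at the documented imbalance.

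The result takes the ICC of 0.01 as given. Table 4 lists values from 0.01 to 0.12, and that choice matters more than anything here: at 0.03, equal clusters give an effective n of 964 and 0.18 SD.

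**What to change.** In Section 2.3.6, state the spread of polyclinic sizes in PROBIT III and compute the effective sample size as Σ mᵢ/(1+(mᵢ-1)×ICC), which matches the random effects analysis. State that the test is two-sided, carry the standardized difference unrounded, and restate both difference columns of Table 5 for cognition, FEV1, FVC, PEFR and LogMAR (the last to three decimals). Alternatively, keep 0.1 SD and state that power is about 70%. In Section 2.3.4.b, say whether 1,000 is the size of the subset or of the clinic.

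The cost is one recalculation from clinic counts that the three earlier phases should already supply, and slightly less favourable figures. It changes neither the analysis nor the number of children.
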